### Statistical analyses

For the qualitative data, we will use Excel 2016 for data input and SPSS 25.0 for statistical analysis. Statistics will include score mean, standard deviation, coefficient of variation, etc. The key basis will be whether it will be used as a common intervention concept for the prevention of comorbidities. Experts will score items with a mean greater than 3.5 and a coefficient of variation less than 0.25. Items will be selected, and the item descriptions will be modified regarding expert suggestions.

For quatitative data, we will double entere by using Epidata 3.1 analyze using SPSS 25.0. The primary outcome will be group differences in changes in visual acuity and body mass index in children and adolescents at 12-month after the baseline. We will use a mixed-effects model to compare the group difference, taking school into account due to its cluster effect. Then we will conduct subgroup analysis to identify the interaction effect (stratification factor × group) and analyze the differences in intervention effects between strata. Furtherly, we will use difference-in-difference analysis to analyze differences between the intervention and control groups before and after the implementation of the intervention. The secondary outcomes will be analysed in the similar steps. All statistical tests will be two-sided at the 5% level of significance.

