**Methods and analysis:**

This study aims to develop a comprehensive intervention strategy "22510SS" based on the socio-ecological model, and A two-arm cluster randomized trial with a parallel-group of a 1:1 allocation ratio in 36 primary and secondary schools to test its evidence-based intervention programs on the effects and implementation of myopia and obesity epidemics in children and adolescents in grades 4 and 7. The primary outcomes will include differences in visual acuity, body mass index, outdoor activity indicators, screen time, fruit and vegetable intake, high-quality protein intake, sugar-sweetened beverage intake, sleep duration, and level of monitoring among children and adolescents. Secondary outcomes will assess the acceptability, feasibility, uptake, use, and maintenance of the intervention. Effects on the primary and secondary outcomes will be analyzed using linear and logistic regression analyses, as well as difference-in-difference analysis, taking into account cluster effects and possible confounding factors. Process assessments will also be conducted through quantitative and qualitative analyses, including acceptability, feasibility, gender, adoption, implementation, and sustainability.

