### Effectiveness evaluation

#### Study design

A two-arm cluster randomized trial with a parallel-group of a 1:1 allocation will be conducted in three districts (Dongcheng District, Tongzhou District, and Changping District) according to their geographical location and socioeconomic conditions in Beijing and then selected schools in the districts for a 12- month intervention. In each of the three districts, 3 primary schools (grades 1–4), 3 junior high schools (junior 1), and a total of 18 schools will be selected as intervention schools, while other 18 schools will be regarded as control schools. t. Children and adolescents grades 1–4 and 7 with aged 6–14 years will be recruited for advoiding missing follow-ups due to further education into other schools (Fig. 4). All intervention schools in the three districts will use a standardized and uniform research protocol.

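### The primary model names no covariate besides school; adding district, school level and the baseline value would cost almost nothing and probably gain precision

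*Protocol article*

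**What the plan says.** The article's Statistical analyses section (effectiveness evaluation) sets the endpoint: "The primary outcome will be group differences in changes in visual acuity and body mass index in children and adolescents at 12-month after the baseline". The next sentence gives the model: "We will use a mixed-effects model to compare the group difference, taking school into account due to its cluster effect". A further step is then planned: "Then we will conduct subgroup analysis to identify the interaction effect (stratification factor × group"), but the factor is not defined and is not placed in the main model. A difference-in-difference comparison follows.

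The Abstract describes the analysis differently. It names linear and logistic regression, "as well as difference-in-difference analysis, taking into account cluster effects and possible confounding factors", and does not say which confounders.

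The Study design section gives the structure: "A two-arm cluster randomized trial with a parallel-group of a 1:1 allocation will be conducted in three districts". The intervention arm is fixed by district and level: "In each of the three districts, 3 primary schools (grades 1–4), 3 junior high schools (junior 1), and a total of 18 schools" are to be the intervention schools. Of the controls it says only "while other 18 schools will be regarded as control schools". The district and level split of the controls is not given, and stratified randomisation is not mentioned.

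**The concern.** The intervention arm consists of six groups of three schools: three districts, each with primary and junior high schools. The protocol gives reasons to expect these groups to differ. The districts were chosen for location and socioeconomic conditions. The two levels cover different ages and have different sleep targets, and their questionnaires are completed with help from different people. A year's change in vision or BMI may well differ between grades 1–4 and grade 7.

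If such differences exist and the model has only a school term, they go into the school variance and enlarge the standard error of the arm effect. With 36 schools, between-school variance is the part that more pupils cannot reduce. A change score also uses the baseline value less efficiently than a model with baseline as a covariate. At stake is precision, not bias and not an excess of false positives.

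**Working it through.** **The plan's own figure.** The article gives no precision or power for visual acuity or BMI. Its only calculation is for co-morbidity (17.3% v 13.5%, two-sided 0.05, 90% power). The printed formula gives 2 × 0.154 × 0.846 × 10.507 / 0.038² = 1896. The unpooled-variance version gives 1891, the stated figure. This calculation does not bear on the model terms. It supplies only the analysed number: 2250 × 0.8 = 1800 pupils per arm, and 1800 / 18 = 100 per school.

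**Not in the documents, so assumed:** the intracluster correlation of change (ρ), the share s of between-school variance due to the six groups, and the baseline-to-12-month correlation r. School sizes are taken as equal.

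**Step 1: district-by-level terms.** Ratio of adjusted to unadjusted standard error:

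√{[ρ(1 − s) + (1 − ρ)/m] / [ρ + (1 − ρ)/m]}, with m = 100.

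At ρ = 0.02 the denominator is 0.02 + 0.0098 = 0.0298. For s = 0.5 the numerator is 0.01 + 0.0098 = 0.0198, so the ratio is √0.664 = 0.815.

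Power in the table starts from an effect for which the school-only analysis would have 0.80 power with a correct standard error on 34 degrees of freedom. The adjusted analysis uses 29 (all six groups fitted).

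The type I errors come from 20,000 simulated trials per setting. They used school means, 18 v 18 schools, the school-only test and a t reference with 34 degrees of freedom. In one version the arms were balanced 3 v 3 within each group; in the other, allocation ignored the groups.

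| s | SE ratio | SE reduction | Power after adjustment | Type I error, balanced | Type I error, not balanced |
|---|---|---|---|---|---|
| 0 | 1.000 | 0% | 0.796 | 0.048 | 0.051 |
| 0.2 | 0.930 | 7% | 0.85 | 0.035 | 0.051 |
| 0.5 | 0.815 | 18.5% | 0.93 | 0.015 | 0.050 |
| 0.8 | 0.681 | 32% | 0.98 | 0.004 | 0.049 |

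In the balanced case with s = 0.5, the estimate's true SD was 0.0472 and the model's mean standard error 0.0577. That gap is what makes the test conservative. Without balance the two agreed (0.0578 and 0.0574).

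To give s a meaning: if the groups differ only by a primary–junior gap of d SD with equal numbers of schools, their variance is d²/4, so d = 2√(sρ). At ρ = 0.02, s of 0.2, 0.5 and 0.8 corresponds to gaps of 0.13, 0.20 and 0.25 SD in 12-month change.

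The range moves with ρ. At s = 0.8 the reduction is 23% for ρ = 0.01 and 43% for ρ = 0.05.

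**Step 2: baseline as covariate.** With equal variances at both times, a change score has variance 2(1 − r)σ² and the baseline-adjusted value (1 − r²)σ². The ratio of standard errors is √[(1 + r)/2].

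| r | SE ratio | SE reduction | Power from 0.80 |
|---|---|---|---|
| 0.5 | 0.866 | 13% | 0.90 |
| 0.7 | 0.922 | 8% | 0.86 |
| 0.8 | 0.949 | 5% | 0.84 |
| 0.9 | 0.975 | 2.5% | 0.82 |
| 0.95 | 0.987 | 1.3% | 0.81 |

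This applies to the arm comparison as far as r is similar at pupil and school level. The gains in steps 1 and 2 were worked out separately and should not be added.

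**The case against.** The model sentence names school because of clustering; it does not exclude other terms. The Abstract promises an analysis "taking into account cluster effects and possible confounding factors", and those factors could include district, level and baseline. A journal article may leave its covariate list to the full analysis plan. This stands in part: the absence of a list is not in itself the defect. But the article does state a primary model, its two descriptions differ, and an open-ended reference to confounders does not secure the design factors.

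Three stronger readings are tempting, and the documents do not support them.

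- A reader might infer that the reported intervals will be too wide and the test well below 5%. That needs balance within district and level in both arms. The article gives the split for the intervention arm only. Without balance, the simulated type I error is 0.049 to 0.051.
- A reader might infer that the baseline value is ignored. It is not: the outcome is change from baseline, and a before–after comparison is also planned. A change score is a valid analysis in a randomised trial. The point is only that baseline is not named as a covariate.
- A reader might infer a large, known loss of power. The size depends entirely on inputs the article does not give. If the groups explain nothing and r is near 1, there is almost nothing to gain.

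**Conclusion.** The point holds as a matter of efficiency. The stated primary analysis is unbiased under random allocation, but it names none of the terms most likely to sharpen it, although the data for them will be at hand.

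The conservative-test result rests on the control schools mirroring three primary and three junior high per district; otherwise adjustment only adds precision. The gains are ranges over assumed inputs, not estimates for this trial.

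The trade is one-sided: if the six groups explain nothing, power falls only from 0.80 to 0.796. This is a free improvement, with moderate confidence. It does not threaten the validity of the trial.

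**What to change.** In Statistical analyses, state one primary model for each of visual acuity and BMI: 12-month value on arm, baseline value, district and school level, with a random intercept for school. Keep the difference-in-difference comparison as a sensitivity analysis with the same school effect. Align the Abstract with this, either by naming the same model or by saying that its confounders are these terms. Also state how the 18 control schools divide by district and level, and whether allocation was stratified on them, since that decides whether the school-only test would be conservative.

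Cost: two degrees of freedom for district and one for level, 3 in all (34 to 31 at school level), or 5 if the six groups are fitted separately (34 to 29). No new data, visits or pupils are needed.

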#### Control group

The children and adolescents in the control schools will have only regular monitoring and class meetings or health education classeswithout clinic doctors’ paricipating.

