***Measurement of indoor environmental indicators***				
Household air pollution exposure	✓	-	✓	Continuous measurement with illuminometer for 7 days
Night light exposure	✓	-	✓	7 consecutive days of measurement with sensors
***Questionnaire***	✓	-	✓	
Student Questionnaire	✓	✓	✓	Issues related to children and adolescents
Parental Questionnaire	✓	✓	✓	Issues related to parents and children
School Questionnaire	✓	✓	✓	School related issues

Anthropometric measures includes visual acuity, refraction,height, weight, waist circumference, hip circumference, blood pressure, blood routine, and body composition, and 5% of the samples were randomly selected for morphological index analysis measurement.

Biospecimen measures consisits of blood, urine of saliva. All biological samples were collected after fasting for 12 h, and biochemical analysis of all biological samples was performed by a biomedical analysis company accredited by Peking University.

Environmental measurements household air pollution exposure and nighttime light exposure.

Questionnaire will be utilized to assess the behaviors of children and adolescents, as well as school policies for the prevention and management of myopia and obesity, along with other possible moderators/mediators of intervention. The questionnaire has been developed based on previous research and pilot studies, and is deemed feasible for this study, as well as acceptable to both children and adolescents and their parents. For children in grades 1–4, parental assistance will be provided to complete the questionnaire, whereas students in grade 7 will receive guidance from their class teacher when filling out the questionnaire.The parent questionnaire will focus on parental information and health behaviors, while the school questionnaire will cover basic information, myopia and obesity intervention work, personnel management, health education, sports activities, nutrition, and classroom environmental sanitation supervision. The trained project members will provide detailed explanations of the questionnaires, and assistance and guidance will be given as needed to complete them effectively. The project team staff will review 3% of the questionnaires within one week.

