### Outcomes

#### Primary outcome

The primary outcome of this study is to assess the differences in changes in visual acuity and body mass index between children and adolescents 12-month after baseline as evaluated by medical examination. Between-group differences in changes in outdoor activities screen time, fruit and vegetable intake, high-quality protein intake, sugar beverage consumption, sleep duration, and supervision will be assessed using questionnaires.

(‘2’). Engage in at least 2 h of outdoor physical activity during the day, with at least 1 h of moderate to high intensity exercise.

(‘2’). Limit screen time to no more than 2 h per day.

(‘5’). Consume 5 servings of fruits and vegetables, each equivalent to an adult’s fist, daily.

(‘1’). Consume 1 serving of lean meat, equivalent to an adult’s hand, daily.

(‘0’). Avoid sugary drinks.

(‘S’). Ensure adequate sleep, with elementary school children needing 10 h and junior high school students needing 9 h of sleep each night.

(‘S’). Parents and students should provide timely feedback and cooperate with efforts to prevent and control myopia and obesity.

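### The abstract names nine primary outcomes and the analysis section two, with every test at 5%, so the plan does not fix which results count as primary success

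*Protocol article*

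**What the plan says.** The primary outcome is described in three places in the protocol article.

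- **Abstract, Methods and analysis.** "The primary outcomes will include differences in visual acuity, body mass index, outdoor activity indicators, screen time, fruit and vegetable intake, high-quality protein intake", and the list then runs on to "beverage intake, sleep duration, and level of monitoring among children and adolescents". That makes nine: visual acuity, BMI, six lifestyle behaviours (outdoor activity, screen time, fruit and vegetables, high-quality protein, sugary drinks, sleep) and monitoring.
- **Outcomes, Primary outcome.** Visual acuity and BMI at 12 months are given as the primary outcome. A further sentence under the same heading adds between-group differences in the six behaviours and in supervision, all assessed by questionnaire.
- **Effectiveness evaluation, Statistical analyses.** "The primary outcome will be group differences in changes in visual acuity and body mass index". The same section ends: "All statistical tests will be two-sided at the 5% level of significance".

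The Secondary outcomes section lists the RE-AIM dimensions and does not name the behaviours or supervision. Under Quantitative data collection, blinding is stated for the staff who measure visual acuity, refraction, height and weight. On the questionnaire, parents assist grades 1–4 and "students in grade 7 will receive guidance from their class teacher when filling out the questionnaire". Supervision as an outcome is described as "Parents and students should provide timely feedback and cooperate with efforts to prevent and control myopia and obesity". Regular supervision is also one of the two S components of the package in Table 2. Control schools "will have only regular monitoring and class meetings" or health education classes, without clinic doctors.

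**The concern.** A reader of the abstract would look for success on any of nine outcomes, and a reader of the analysis section on two. Each version leads to a different claim, and every test is run at 5% either way. Followed as written, the trial could report a positive primary outcome on a questionnaire item while both blind-measured health outcomes show nothing.

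The seven additional outcomes are also those most open to reporting bias. The people who help to complete the answers are, in the intervention arm, asked to encourage and supervise the behaviour being reported. Supervision is both delivered and measured, so a between-arm difference in it would partly describe delivery and not benefit.

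**Working it through.** **1. The lists side by side.**

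| Place | Visual acuity, BMI | Six behaviours | Supervision or monitoring |
|---|---|---|---|
| Abstract | primary | primary | primary |
| Primary outcome section | primary | under the primary heading | under the primary heading |
| Statistical analyses (effectiveness) | primary | not named | not named |
| Secondary outcomes section | not named | not named | not named |

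The seven questionnaire outcomes therefore have no explicit place except as primary.

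**2. Chance of at least one false positive.** Inputs: k outcomes, no true effect on any, each tested at two-sided 0.05 (Statistical analyses), and success meaning any one significant. That success rule is an assumption; the article does not state one.

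- Nine independent outcomes: 1 − 0.95^9 = 0.370. Favourable direction only: 1 − 0.975^9 = 0.204.
- Two independent outcomes: 1 − 0.95^2 = 0.0975. Favourable direction only: 1 − 0.975^2 = 0.049.

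The outcomes are unlikely to be independent, and the article gives no correlations. Simulating nine equally correlated test statistics (400,000 sets) over an assumed range gives:

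| Assumed correlation | Either direction | Favourable only |
|---|---|---|
| 0.2 | 34.8% | 18.0% |
| 0.3 | 32.6% | 16.5% |
| 0.5 | 26.8% | 13.4% |
| 0.7 | 20.2% | 10.1% |
| 0.9 | 12.3% | 6.2% |

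**3. Blinding and overlap with the intervention.** The stated blinding covers the measurements behind visual acuity and BMI and does not mention questionnaires. Table 3 gives parents and teachers, including classroom teachers, a supervising and guiding role in the intervention. Parents and class teachers are the people who help with the student questionnaire. Table 7 delivers supervision through regular health-behaviour questionnaires, monitoring and feedback on WeChat, and the outcome is timely feedback and cooperation. The Process evaluation section already has an element for this, dose received (exposure).

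**4. What a split of alpha would cost.** The article gives no power for visual acuity or BMI, so only its co-morbidity calculation (Sample size) can serve as an illustration. Inputs: 17.3% versus 13.5%, two-sided 0.05, 90% power.

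- Unpooled variance: (0.173 × 0.827 + 0.135 × 0.865) × (1.960 + 1.2816)² / 0.038² = 1890.8, which gives the stated 1891 per arm. The pooled formula printed in the article gives 1896, which is close.
- Standardised difference at 1891 per arm: 0.038 / √(0.2598/1891) = 3.242.
- Power at 0.05: Φ(3.242 − 1.960) = 90.0%.
- Power at 0.025: Φ(3.242 − 2.241) = 84.1%.

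These power figures ignore clustering by school.

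**The case against.** The strongest reply is that the body of the article is fairly clear. Both the Primary outcome section and the analysis section use the term primary outcome for visual acuity and BMI, the behaviours come in a separate sentence, and the nine-item list stands only in the abstract. This stands in part: two outcomes is the better reading. It does not settle the matter, because the shared heading and the silence of the Secondary outcomes section both support the abstract. The RE-AIM analysis text does count behaviour indicators under Effectiveness, but it counts physical indicators there too, so it cannot separate the two groups.

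A second reply is that a multiplicity rule may sit in an analysis plan that is not shown. That is fair, and its absence here is not the point. The point is that the published text gives two primary sets, and any later plan that picks one will contradict part of it.

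A third reply is that behaviour change belongs to main objective (i), so ranking the behaviours second is a design choice. That is also fair. Any single list used throughout would remove the contradiction; the recommendation for two rests on the blinding and on the article's own analysis section.

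Three stronger readings are tempting and are not supported:

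- **That a false primary success is likely.** Multiplicity alone gives at most 37%, under a success rule the article does not state, and about 20% in the favourable direction. Bias in the questionnaires could add to this, but the documents do not allow it to be sized.
- **That a difference in supervision follows automatically from allocation.** Controls also get regular monitoring, the outcome is taken by questionnaire and not from applet logs, and the items are not shown. A difference is to be expected but is not certain.
- **That the questionnaires are declared unblinded.** The article is silent; this is inferred from who answers and who helps.

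**Conclusion.** The point holds as a contradiction in the primary outcome set: nine in the abstract, two in the analysis section, and two plus seven under one heading in between, with all tests at two-sided 5%. If any one result counted, the chance of at least one false positive would be up to 37% for nine independent outcomes, about 27% at an assumed correlation of 0.5, and about 20% for independent outcomes counting only favourable results. For two it would be 9.75%, or 4.9% favourable. These figures rest on the any-one rule and on assumed correlations.

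The consequence is greater because the seven disputed outcomes fall outside the stated blinding and one of them overlaps with the intervention. How much bias that brings cannot be put in numbers from the article. The point should be corrected, but it does not undermine the two blind-measured outcomes.

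**What to change.** In the abstract, the Primary outcome section and the analysis section:

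- Name 12-month change in visual acuity and in BMI as the only primary outcomes.
- Test them with Holm at an overall two-sided 5%: the smaller p-value against 2.5% and, if that passes, the other against 5%.
- List the six lifestyle behaviours as secondary outcomes.
- Report supervision under process evaluation, as dose received.

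The cost is wording and some power, since the smaller primary p-value has to meet 2.5%. The loss should be modest but cannot be quantified for visual acuity or BMI, because the article gives no power for them. On the co-morbidity endpoint, ignoring clustering, 90% falls to about 84%.

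No change is proposed to who guides the grade 7 questionnaire. Moving this to project staff would not remove the bias, because they also deliver parts of the intervention and grades 1–4 would still rely on parents. Baseline collection was also scheduled for March 2023, before the article appeared.
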